#### **Day 112:**

The following procedures will be performed:

- Record concomitant medications, including statin (standard care) , dose plus adherence for prior month
- Obtain body weight
- Record vital signs (blood pressure, heart rate, respiratory rate, and temperature);
- Collect fasting blood samples for Lipid profile

#### **Laboratory Investigations:**

All screening and on-study laboratory samples will be processed and sent to Biochemistry Department ,AIIMS, Bhubaneswar The results of this testing will be maintained in the source documents at the site. The date and time of sample collection will be recorded in the source documents at the site. At screening, laboratory investigations such as hematology (WBC, Hb, RBC, Hematocrit, Platelets, Differential Leucocyte Count), HbA1C, lipid profile, LFT, RFT, Thyroid profile would be done to rule out any systemic pathology, following which the participant would undergo an ECG. The results will be carried over to baseline and it is expected that the gap between screening and baseline visit is less than 2 days. Adiponectin, ghrelin, apolipoprotein A1 and apolipoprotein B, Hs-CRP, IL-6 would be assessed on baseline. Stool sample would be collected for

gut microbiome analysis at baseline and day 90. The laboratory investigations would again be done on day 90.

### **Sample Size and statistical considerations:**

Sample size: 85 per group and a total of 170 participants

The sample size for the study has been calculated considering the mean change in LDL-c levels after treatment.. A previous study on the efficacy and safety of atorvastatin in patients with hypercholesterolemia denoted a change of 35% after treatment in LDL-c levels. We hypothesized a change of at least 45% in the LDL-c levels after treatment in patients treated with atorvastatin + trial intervention as add-on. Therefore, a mean change of 14 mg/dl (equivalent to absolute difference of 10% change between both the groups) in LDL-c levels after treatment between both groups will be considered as clinically relevant, with a standard deviation of 30 mg/dl based on the results of the above quoted study, with 80% power and 5% level of significance, a sample size of 72 participants per group was calculated. Adding an attrition rate of 20%, the final sample size was set at 85 participants per group. Therefore, a total of 170 participants will be enrolled in the study.

$$k=n_2/n_1=1$$

$$n_1=(\sigma_1^2+\sigma_2^2/K)(z_{1-\alpha/2}+z_{1-\beta})^2/\Delta^2$$

$$n_1= (302+302/1)(1.96+0.84)^2/142$$

$$n_1=72$$

$$n_2=K \cdot n_1=72$$

(Reference: Kim JB, Song WH, Park JS, Youn TJ, Park YH, Kim SJ, Ahn SG, Doh JH, Cho YH, Kim JW. A randomized, open-label, parallel, multi-center Phase IV study to compare the efficacy and safety of atorvastatin 10 and 20 mg in high-risk Asian patients with hypercholesterolemia. *PLoS One*. 2021 Jan 22;16(1):e0245481. doi: 10.1371/journal.pone.0245481. Erratum in: *PLoS One*. 2021 Oct 20;16(10):e0259072. PMID: 33481866; PMCID: PMC7822387)

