**Intervention:**

**Group I :** Tablet Trikatu 1000 mg twice daily with luke warm water one hr after food for 12 weeks along with standard care (Statins)

**Group II:** Matching placebo 1000 mg twice daily with luke warm water one hr after food for 12 weeks along with standard care (Statins)

The participants in both groups will receive standard care as per the 2019 ACC/AHA

**Duration of intervention:** 12 weeks (84 days)

**Sample size:** 85 per group (Total 170)

**Study Population:** Patients with Dyslipidemia diagnosed based on the 2019 ACC/AHA Guideline on the Primary Prevention of Cardiovascular Disease.

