### **Randomization procedure**

Block randomization list with unequal block sizes will be generated to randomize the participants to either receive intervention or a matching placebo in the ratio of 1:1. The packaging of the intervention and placebo will be done as per the randomization list and will maintain concealment and double blinded treatment allocation. After randomization neither the participant nor the investigator will be aware of the treatment allocation. Only the statistician who will generate the randomization sequence will be aware of the treatment allocation, and will keep the sequence sealed till the completion of the study.

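### 85 per group does not allow for the stated 20% attrition: it leaves 68 evaluable per group and about 77% power, not 80%

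*Protocol*

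**What the plan says.** The Protocol section on sample size and statistical considerations bases the calculation on the change in LDL cholesterol. The target is "a mean change of 14 mg/dl (equivalent to absolute difference of 10% change between both the groups"), "with a standard deviation of 30 mg/dl based on the results of the above quoted study". It continues: "with 80% power and 5% level of significance, a sample size of 72 participants per group was calculated". The attrition step follows: "Adding an attrition rate of 20%, the final sample size was set at 85 participants per group". The section ends: "Therefore, a total of 170 participants will be enrolled in the study". The Protocol summary repeats 85 per group and 170 in total. The randomisation section allocates participants "to either receive intervention or a matching placebo in the ratio of 1:1".

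Three other places bear on what happens to participants who are lost. The withdrawal criteria say that those who withdraw may not be replaced. The statistical analyses section says that missing data are not imputed. The primary outcome is the change in LDL cholesterol between week 0 and week 12.

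**The concern.** The number to enrol should be the evaluable number divided by the fraction expected to remain. The step from 72 to 85 is too small for a 20% loss under either rule in common use. The Protocol therefore promises more protection against dropout than 170 participants give.

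If attrition reaches the level the sponsor planned for, the trial will fall below its own evaluable target. With no replacement and no imputation, the sample size section offers nothing to make up the difference. The enrolled number, the power and the attrition allowance are all fixed in the Protocol, so a later analysis plan cannot make them agree.

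**Working it through.** **Inputs**, all from the sample size section unless noted:
- difference in mean LDL change Δ = 14 mg/dl
- SD σ = 30 mg/dl in both groups
- two-sided α = 5% (z = 1.96)
- power 80% (z = 0.84)
- allocation 1:1 (randomisation section)
- attrition 20%
- enrolled 85 per group

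**1. The Protocol's own figure.**
n = (σ² + σ²)(1.96 + 0.84)²/Δ² = (900 + 900) × 7.84/196 = 72.0 per group.
The stated 72 reproduces exactly. In the printed formula, 302 and 142 are 30² and 14² with the superscripts lost, so they are not errors. Unrounded z values give 73, a trivial difference.

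**2. Allowance for attrition.**
- Correct inflation: 72/(1 − 0.20) = 90 per group, 180 in total. Starting from 73 it is 92 per group, 184 in total.
- Common shortcut: 72 × 1.20 = 86.4, so 87 per group.
- Stated: 85, which is below both. It is an uplift of 85/72 − 1 = 18%.

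**3. What 85 per group delivers.**
- Evaluable after a 20% loss: 85 × 0.80 = 68 per group.
- Largest attrition that still leaves 72: 1 − 72/85 = 15.3%.

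**4. Power.** By the normal formula, power = Φ(Δ/(σ√(2/n)) − 1.96). At n = 68 the standard error is 30 × √(2/68) = 5.145, so the power is Φ(14/5.145 − 1.96) = Φ(0.761) = 77.7%. The t-test column uses the noncentral t distribution.

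| Evaluable per group | Normal formula | t-test |
|---|---|---|
| 68 (85 enrolled, 20% lost) | 77.7% | 77.1% |
| 72 (the Protocol's target) | 80.0% | 79.4% |
| 85 (no losses) | 86.0% | 85.7% |

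Like for like, the loss from 72 to 68 is about 2.3 points by either method.

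**5. Detectable difference at 80% power with 68 per group.**
2.80 × 5.145 = 14.4 mg/dl, against 14.0 mg/dl at 72.

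**The case against.** The arithmetic itself is hard to dispute. The case on the other side concerns how much it matters.

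- **The loss is small.** It is about 2.3 points of power and 0.4 mg/dl in detectable difference. The SD is a round figure taken from another study, and a true SD of 30 × √(68/72) = 29.2 mg/dl would cancel the whole effect. This stands, and it limits the weight of the point. It does not make 85 follow from 72 and 20%.
- **68 is the worst case.** The withdrawal section encourages people who stop the intervention to stay for data collection, and the section on protocol violations says that all included participants are followed up. Some attrition cases may therefore still provide a week-12 value. This also stands. But 20% is the loss the sponsor chose to plan for, and the calculation takes no credit for retention.
- **Covariate adjustment could recover the loss.** In a linear analysis that reduces the SD by √(1 − r²), a correlation of r = √(1 − 68/72) = 0.24 would be enough. The Day 28 and Day 56 lipid values might also help. The sample size section relies on neither, so they cannot justify its number.
- **The figures are for a comparison of means, while the statistical analyses section names ordinal logistic regression.** That is a fair limit. The figures test the sample size section on its own terms. They do not give the power of the planned model.

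**Conclusion.** The statement is wrong as written. On the Protocol's own assumptions, 85 per group with 20% attrition leaves 68 evaluable, with power of 77.7% (normal formula) or 77.1% (t-test). Meeting the stated claim takes 90 per group, so the shortfall is 5 per group and 10 in total. The error does not invalidate the trial.

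The conclusion takes the 14 mg/dl difference and the 30 mg/dl SD as given, and it assumes that a participant lost to attrition contributes no week-12 LDL value.

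**What to change.** Replace the attrition sentence in the sample size section with wording such as:

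> With 85 participants enrolled per group, the trial has 80% power if attrition does not exceed 15% (72 evaluable per group). At 20% attrition (68 evaluable per group), power is about 77%.

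This costs one sentence and a slightly less favourable claim. The enrolment target, the design and the Protocol summary stay as they are.

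If the sponsor prefers to keep both 20% attrition and 80% power, the target becomes 90 per group and 180 in total. The sample size section and the Protocol summary must then change together, and ten more participants must be recruited and funded. The budget gives a mixed picture on that:

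- **Laboratory table.** It is headed for 170 participants, but most priced lines work out at 204 (lipid profile 127,500/(125 × 5) = 204; gut microbiome 3,264,000/(8,000 × 2) = 204). The blood count line gives 7,440/(15 × 2) = 248. The reason for the uplift is not stated, so it should not be counted on without checking.
- **Atorvastatin and travel support.** Both are priced for 170. At the budgeted Rs 2,250 per person, atorvastatin for 180 comes to Rs 405,000 against Rs 400,000 allotted. Travel support would rise by 100 × 5 × 10 = Rs 5,000.

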### **Statistical analyses:**

A detailed Statistical Analysis Plan will be drawn up before breaking the randomisation code. We will analyse the data according to the intention-to-treat principle. Clinical outcome and laboratory outcome will be compared between the study groups by means of ordinal logistic regression, after adjustment for covariates.

We will perform pre-specified subgroup analyses of participants based on their risk as per the FRS, co-morbidities like DM, HTN, dose of standard care etc. Summary statistics by each treatment group will be tabulated at each visit. For continuous endpoints, the descriptive statistics include number of participants, mean, median, standard deviation, standard error, lower and upper quartiles, minimum, and maximum. For categorical endpoints, frequency, and percentage will be given. Missing data will not be imputed

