#### **Outcome Measures:**

##### **Primary Outcome Measure:**

- Change in fasting serum LDL cholesterol [ Time Frame: 0, 12 weeks ]

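### The protocol names ordinal logistic regression for all clinical and laboratory outcomes, but the primary outcome is a continuous LDL-C change and the trial is sized on a 14 mg/dl difference in means

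*Protocol*

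**What the plan says.** - **Endpoint.** Protocol, Primary Outcome Measure: "Change in fasting serum LDL cholesterol [ Time Frame: 0, 12 weeks". This is a laboratory value in mg/dl. No ordered LDL-C categories are defined anywhere in the protocol.
- **Sizing.** Protocol, Sample Size and statistical considerations: "The sample size for the study has been calculated considering the mean change in LDL-c levels after treatment". The target is "a mean change of 14 mg/dl (equivalent to absolute difference of 10% change between both the groups", "with a standard deviation of 30 mg/dl based on the results of the above quoted study". The result is given as "with 80% power and 5% level of significance, a sample size of 72 participants per group was calculated".
- **Analysis.** Protocol, Statistical analyses: "Clinical outcome and laboratory outcome will be compared between the study groups by means of ordinal logistic regression, after adjustment for covariates". LDL-C is a laboratory outcome, so the primary endpoint falls under this sentence. In the same section, means, SDs and quartiles of continuous endpoints appear only as descriptive summaries by group and visit. Detail is deferred to a statistical analysis plan to be written before the code is broken.

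**The concern.** The endpoint, the sample size and the analysis should refer to the same quantity. Here the first two refer to a difference in mean LDL-C change, and the third refers to a cumulative odds ratio. Three things follow.

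1. The main result would be on a scale that cannot be read directly against the 14 mg/dl target.
2. The 80% power was calculated for a comparison of means, not for the named model.
3. If the model is applied in its usual form, LDL-C must be cut into ordered classes. As the protocol states none, the cut-points stay open.

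This is more than detail left to the analysis plan. The protocol has already named the model. An analysis plan that follows it inherits the mismatch, and one that departs from it contradicts the protocol.

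**Working it through.** **Inputs from the protocol.** Difference 14 mg/dl; SD 30 mg/dl in each group; two-sided 5% (z = 1.96); 80% power (z = 0.84); 1:1 allocation (Randomization procedure: "to randomize the participants to either receive intervention or a matching placebo in the ratio of 1:1").

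**Step 1. Reproduce the stated size.** n = (30² + 30²) × (1.96 + 0.84)² / 14² = 1800 × 7.84 / 196 = 72.0 per group. Unrounded z values give 72.08, so 73. The formula as it reads here ends "1.96+0.84)^2/142"; the 142 is 14² with its superscript lost, and the 302 is likewise 30². Taken literally those figures would give (302 + 302) × 7.84 / 142 = 33, which is not the stated result. The 72 is therefore a two-sample comparison of means.

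**Step 2. Power of that comparison.** SE = 30 × √(2/72) = 5.0; 14/5.0 = 2.8; power = Φ(2.8 − 1.96) = Φ(0.84) = 80%.

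**Step 3. What the named model estimates.** A shift of 14 mg/dl with SD 30 and a shift of 7 mg/dl with SD 15 are the same standardised shift: 14/30 = 7/15 = 0.467. Both give a log odds ratio of about 0.467 × 1.702 = 0.79 and a concordance of Φ(0.467/√2) = 0.629. The odds ratio alone does not separate a 14 mg/dl effect from a 7 mg/dl effect.

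**Step 4. Power of the ordinal test.** Assumptions, none of them in the protocol: normal data, no covariates, and either every value kept as a rank or k equal-sized classes with equally spaced scores. The efficiency relative to the comparison of means is e = [Σφ(c_j)]² / [(k² − 1)/12], with c_j = Φ⁻¹(j/k); for ranks e = 3/π. Power = Φ(2.8√e − 1.96).

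| LDL-C kept as | e | 2.8√e − 1.96 | Power, 72 per group | Simulated |
|---|---|---|---|---|
| Comparison of means | 1 | 0.84 | 80% | 79.4% (exact t-test, not simulated) |
| Ranks, no grouping | 3/π = 0.955 | 0.776 | 78% | 76% |
| 4 classes | 1.0345²/1.25 = 0.856 | 0.631 | 74% | 72% |
| 3 classes | 0.7272²/0.6667 = 0.793 | 0.534 | 70% | 68% |
| 2 classes | 0.3989²/0.25 = 0.637 | 0.274 | 61% | 61% |

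The last column comes from 4,000 simulated trials per row of the tie-corrected rank-sum test, which is the score test of a proportional-odds model without covariates. It runs up to about 2 points below the approximation and shows the same pattern.

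**Step 5. Effect of the fix on n.** With a comparison of means the sizing applies as written: 80% at 72 per group. With all 85 per group analysed, SE = 30 × √(2/85) = 4.60, 14/4.60 = 3.04, and power = Φ(1.08) = 86%. Both figures are before any gain from baseline adjustment.

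**The case against.** Four points can be made for the plan as written.

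**The ordinal model need not group LDL-C.** It can be fitted with each observed value as its own level, and fitted means can then be derived from it. The test for a treatment difference also remains valid. This stands. A reader might infer that the named analysis cannot estimate the 14 mg/dl target at all, and that goes too far. What the text supports is that the model's own effect measure is an odds ratio and that the protocol describes no step back to mg/dl.

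**The power loss may be small.** This also stands. The section mentions no cut-points, and it lists means and quartiles for continuous endpoints. Without grouping the loss is about 2 to 3 points. Only coarse grouping makes it material, and that is an assumption about what would be done.

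**The ordinal model is to be covariate-adjusted.** A reader might set the figures in the table against a baseline-adjusted linear model and conclude that the named method gives up far more power. The documents do not support that comparison. The named analysis already promises covariate adjustment, and although the covariates are not listed, baseline LDL-C could be one. Most of the gain from baseline adjustment is open to either model.

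**The analysis plan could settle it.** It could add detail, but it cannot choose a different type of model without contradicting the protocol. This objection does not remove the point.

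Nor does the sentence need replacing for every outcome. For the binary outcome (total cholesterol below 200 mg/dl) an ordinal model reduces to ordinary logistic regression. For markers that may be skewed, such as hs-CRP or IL-6, a rank-type model can be reasonable.

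**Conclusion.** The mismatch is real and lies in the protocol's own text: a continuous primary endpoint and a means-based sample size, paired with an odds-ratio model as the only between-group analysis named. The firm conclusion is about scale. The primary result would not directly estimate the difference on which the trial was designed, and the stated 80% power was not derived for that analysis.

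The effect on power is conditional. Under normal data, a shift of 14 mg/dl, SD 30, 72 per group and no covariates, it ranges from about 2 points (80% to 78%) with no grouping to about 19 points (80% to 61%) with two equal classes. The documents do not say which would apply. They therefore do not support a claim that the trial is seriously underpowered, only that its stated power does not describe the stated analysis.

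**What to change.** For the primary outcome, replace the sentence in Statistical analyses with a linear model of week-12 fasting LDL-C that has treatment and baseline LDL-C as terms: an ANCOVA, or a mixed model for repeated measures using the scheduled lipid profiles. Report the adjusted mean difference in mg/dl with a 95% CI, so that it can be read against 14 mg/dl. Limit ordinal regression to outcomes that are truly ordinal, and leave the models for the remaining outcomes to the statistical analysis plan.

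The cost is a wording amendment before unblinding. The lipid profile is already taken at screening (and carried over to baseline), Day 28, Day 56 and Day 84. The change requires no new sample size, visits or data.

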#### **Day 28, Day 56:**

The following procedures will be performed:

- Record concomitant medications, including statin (standard care) , dose plus adherence for prior month;
- Obtain body weight, BMI, Waist circumference
- Record vital signs (blood pressure, heart rate, respiratory rate, and temperature)
- Collect fasting blood samples for Lipid profile
- Provide trial drug for 28 days;
- Assess adverse events and compliance to the trial intervention for the past 28 days

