### **Withdrawal Criteria**

Participation of a subject in this clinical study is entirely voluntary and may be discontinued for any of the following reasons:

- The subject withdraws consent or requests discontinuation from the study for any reason;
- Occurrence of any medical condition or circumstance that exposes the subject to substantial risk and/or does not allow the subject to adhere to the requirements of the protocol;
- Any serious adverse event (SAE), clinically significant adverse event, severe laboratory abnormality, or other medical condition which indicates to the Investigator that continued participation is not in the best interest of the subject;
- Pregnancy;
- Subject failure to comply with protocol requirements or study-related procedures
- Poor compliance
- Termination of the study by the Sponsor or the regulatory authority.

If a subject discontinues prematurely from the study due to the above criteria or any other reason, study staff should make every effort to document the clinical evaluations as far as possible in the electronic case report form (eCRF).

Withdrawn subjects may not be replaced. Withdrawal of consent for a study means that the subject does not wish to receive further protocol-required therapies or procedures, and the subject does not wish to or is unable to continue further study participation.

If a participant wishes to discontinue receiving the trial interventions, they will be encouraged to remain in the study for the purposes of data collection in line with the study schedule. If they wish to discontinue data collection, they will be asked to participate in an 'end of study' assessment at the time of withdrawal. Data collected prior to withdrawal will be used in the study analysis unless consent for this is specifically withdrawn. Should a decision to withdraw from the study be made, a reason for withdrawal will be sought but participants and/or carers can choose to withdraw without providing an explanation.

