### **Handling of protocol violations and protocol amendments**

The nature and reasons for the protocol violation shall be recorded in the CRF, in the source documents and in the monitoring visit report. In parallel, corrective and/or preventive actions will be undertaken and documented, including any retraining of the investigator and site staff. All participants who have been included in the trial will be followed up, irrespective of whether treatment was discontinued prematurely, or whether the protocol was violated.

All important changes to the trial will be specified in protocol amendments. Amendments must be approved by the Sponsor, and the PI has the responsibility to seek approval from the competent authorities the ethics committees. The approval shall also be conveyed to the sponsor

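### Intention to treat is promised, but the stated endpoint, regression and no-imputation rule leave an available-case analysis of participants with a Day 84 LDL-C, and the follow-up rules conflict

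*Protocol*

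**What the plan says.** **Analysis.** The Protocol, Statistical analyses, says "We will analyse the data according to the intention-to-treat principle". Outcomes are to be "compared between the study groups by means of ordinal logistic regression, after adjustment for covariates". The section closes with "Missing data will not be imputed". It defers detail to a statistical analysis plan to be written before unblinding, which is not at hand.

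**Endpoint and data.** The primary outcome is "Change in fasting serum LDL cholesterol [ Time Frame: 0, 12 weeks". Lipids are also measured between those points: under Day 28, Day 56 the instruction is "Collect fasting blood samples for Lipid profile". The Schedule of Assessments and the laboratory budget both list these samples.

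**Withdrawal and follow-up.** Withdrawal Criteria lists reasons for which participation in the study may be discontinued. They include "Subject failure to comply with protocol requirements or study-related procedures" and, as a separate item, poor compliance. The same section says "Data collected prior to withdrawal will be used in the study analysis unless consent for this is specifically withdrawn". Handling of protocol violations and protocol amendments says "All participants who have been included in the trial will be followed up, irrespective of whether treatment was discontinued prematurely", and extends this to protocol violations.

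**Attrition.** Sample Size and statistical considerations computes 72 per group, allows for 20% attrition and sets 85 per group.

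**The concern.** A participant with no Day 84 LDL-C has no week 0-to-12 change. If no value may be imputed and the regression has no repeated-measures structure, that participant cannot contribute to the primary comparison. The plan expects this for up to one participant in five, so the analysis as written does not deliver the promised comparison of everyone randomised.

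Two further passages pull against this. Withdrawal Criteria promises that data collected before withdrawal will be used, yet the named method gives the Day 28 and Day 56 LDL-C no route into the primary comparison. And sites are told both that study participation may end for non-compliance and that all included participants are followed up regardless. The first rule lets Day 84 values go missing for a reason that arises after randomisation and may relate to tolerability or response.

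At stake are the validity of the primary estimate if dropout is selective, and some power even if it is not.

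**Working it through.** **Inputs from the Protocol:** difference 14 mg/dl, SD 30 mg/dl, two-sided 5% level, 80% power, 72 per group computed, 20% attrition, 85 per group enrolled.

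**1. The Protocol's own figure.** n = (30² + 30²)(1.96 + 0.84)² / 14² = 1800 × 7.84 / 196 = 72.0 per group. This reproduces the stated 72 (73 with unrounded normal quantiles).

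**2. Participants left at Day 84.** 0.20 × 85 = 17 lost per arm; 85 − 17 = 68 remain. The 85 is close to 72 × 1.2 = 86.4, whereas 72 / 0.8 = 90. That arithmetic is a separate issue, but it is why 68 falls below 72.

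**3. Power, with the Protocol's comparison of means:** Φ(14 / (30√(2/n)) − 1.96).

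| n per arm | Standard error (mg/dl) | Power |
|---|---|---|
| 85 | 4.602 | 86.0% |
| 72 | 5.000 | 80.0% |
| 68 | 5.145 | 77.7% |

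**4. Bias, by simulation.** These settings are assumptions, not Protocol figures: LDL-C reduction at Days 28, 56 and 84 with SD 30 mg/dl, constant within-person correlation of 0.5 or 0.7, 85 per arm, 4,000 runs per scenario. About 20% per arm lose Day 84 but keep Days 28 and 56. In the selective scenario, Trikatu participants with a poor Day 56 reduction are more likely to leave, and placebo dropout is random. The available-case Day 84 comparison is set against a likelihood model using all visits, with its covariance taken as known.

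| Dropout | Correlation | True difference | Available-case: mean, rejection rate | All visits: mean, rejection rate |
|---|---|---|---|---|
| Random | 0.5 | 14 | 14.1, 78.2% | 14.1, 81.1% |
| Random | 0.7 | 14 | 14.0, 77.9% | 14.0, 82.8% |
| Random | 0.5 | 0 | −0.1, 6.3% | −0.1, 5.5% |
| Random | 0.7 | 0 | −0.1, 5.0% | 0.0, 4.8% |
| Selective | 0.5 | 14 | 16.8, 90.7% | 13.9, 79.4% |
| Selective | 0.7 | 14 | 18.2, 95.0% | 14.0, 83.2% |
| Selective | 0.5 | 0 | 2.9, 8.9% | 0.0, 5.1% |
| Selective | 0.7 | 0 | 4.2, 13.5% | 0.1, 5.2% |

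Random dropout causes no bias and costs about 3 to 5 points of power relative to using all visits. One-sided selective dropout inflates the available-case estimate by about 3 to 4 mg/dl. The scenario favours the all-visit model, because dropout depends only on an observed Day 56 value and every dropout keeps the two earlier values.

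**5. An illustration of what the model alone would not correct.** If the 20% who leave gained no add-on benefit, the all-randomised difference would be 0.8 × 14 = 11.2 mg/dl, against 14 among those who stay; 14 / 11.2 = 1.25. A model that assumes data missing at random treats leavers like similar participants who remain in their arm. It would therefore tend towards 14 unless earlier LDL-C already showed the loss.

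**The case against.** The strongest reply is that the model's time structure, the handling of a missing Day 84 value and sensitivity analyses belong in the statistical analysis plan, which the Protocol promises. That stands for detail. It does not dispose of the point, because the Protocol itself fixes a method and a rule: a later plan that imputed, even as a sensitivity analysis, would contradict the rule read at face value. The sentence does close a paragraph on descriptive statistics, so its reach over the primary comparison is arguable. That is a reason to clarify it.

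It is also true that not imputing does no harm by itself. A repeated-measures model needs no imputation. The difficulty lies in combining the rule with a single-time-point comparison.

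A reader might infer more than the text supports, in three ways:

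- *That the trial becomes an analysis of compliant completers.* Discontinuation for poor compliance is permissive. Those who choose to stop treatment are encouraged to continue with data collection, and those who leave are asked for a final assessment. Investigator Responsibilities for Data Collection covers people not receiving protocol therapy. A non-complier with a Day 84 LDL-C stays in the analysis.
- *That the Day 28 and Day 56 LDL-C are wasted.* They are tabulated by visit, and pre-withdrawal data are promised a use. What is missing is a route into the primary comparison.
- *That the effect will be overstated by 25%.* The 14 versus 11.2 mg/dl contrast assumes that everyone who leaves gains nothing. The Protocol gives an overall attrition rate and no reasons for leaving.

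**Conclusion.** The point holds in a limited form. As written, the primary comparison is an available-case analysis of participants with a Day 84 LDL-C, which does not match the intention-to-treat commitment. At the planned attrition it rests on 68 per arm, with about 77.7% power under the Protocol's own assumptions.

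Whether it is biased depends on why people leave. It is unbiased if dropout is random. It is biased if dropout depends on response or tolerability and differs between arms. The 3 to 4 mg/dl from the simulation is illustrative: it rests on assumed correlations of 0.5 to 0.7 and on selective dropout in one arm only, and other mechanisms would change its size and direction.

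The conflict between Withdrawal Criteria and Handling of protocol violations and protocol amendments is real whatever the dropout mechanism, and must be reconciled.

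**What to change.** 1. **Primary analysis.** State it as a likelihood-based mixed model for repeated measures of LDL-C at Days 28, 56 and 84, with terms for treatment, visit, treatment-by-visit and baseline LDL-C. Include all randomised participants with any post-baseline value and report the Day 84 difference. Report by arm how many have no post-baseline value, since this model cannot include them.
2. **No-imputation sentence.** Keep it for the primary analysis, but limit it to that analysis. Add a placebo-based or delta-adjusted multiple-imputation sensitivity analysis.
3. **Follow-up.** Reconcile Withdrawal Criteria with Handling of protocol violations and protocol amendments. Separate ending data collection from stopping trial product, and seek a Day 84 LDL-C from every randomised participant who has not withdrawn consent. Whether product is stopped remains a clinical decision.

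Items 2 and 3 matter as much as item 1, because the mixed model would not in general close a gap such as 14 versus 11.2 mg/dl. That needs Day 84 values from those who stop, and the sensitivity analysis.

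The cost is a wording change before unblinding, some extra analysis, and staff effort to obtain Day 84 visits. No new samples are needed.
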